### Trial design {8}

The STOPPIT trial is an investigator-initiated, prospective, multicentre, randomized, placebo-controlled, double-blind, parallel-group trial. It is designed to demonstrate superiority of PPI discontinuation over PPI continuation in patients with liver cirrhosis. Figure 1 illustrates the trial design. In total, 476 patients will be randomized (1:1) to discontinue PPI therapy and receive placebo or to continue PPI therapy with esomeprazole 20 mg/day over a period of 360 days.

**Fig. 1 Fig1:**
[figure not shown]
Flow chart of the STOPPIT trial. Please note, only key inclusion and exclusion criteria are depicted into this flow chart. Full in- and exclusion criteria are to be found in Table 1

## Methods: participants, interventions and outcomes

### Study setting {9}

The clinical trial takes place in 18 university hospitals throughout Germany. The list of participating sites can be obtained on ClinicalTrials.gov (NCT04448028) and in the German Clinical Trials Registry (DRKS00021290). Each site has a high level of experience in the treatment of patients with liver cirrhosis and in conducting trials.

### Eligibility criteria {10}

Hospitalized, or recently hospitalized, patients with liver cirrhosis with a pre-existing long-term PPI therapy will be screened. Patients with an evidence-based indication for PPI therapy, for example, recent diagnosis of severe reflux esophagitis (LA grade C or D) or peptic ulcers are excluded (for details see Table 1).

**Table 1 Tab1:** In- and exclusion criteria. Patients can be included in the trial, if they fulfil all the inclusion and none of the exclusion criteria

Inclusion criteria	Exclusion criteria
Male and female patients, at least 18 years old.	Diagnosis of reflux esophagitis LA grade C or D by EGD < 2 months prior to the screening visit without PPI therapy for at least 8 weeks prior to the screening visit.
Patients with liver cirrhosis. The diagnosis of liver cirrhosis may be based on (i) histology or (ii) a combination of clinical, laboratory and radiological criteria.	Peptic ulcers diagnosed by EGD < 28 days prior to the screening visit.
Hospitalization or recent hospitalization (0 to 42 days prior to the baseline visit) with complications of liver cirrhosis.	History of endoscopic therapy for oesophageal varices < 14 days prior to the screening visit.
Treatment with PPI for at least 28 days prior to screening.	Life-expectancy < 1 year (at the discretion of the investigator) due to extrahepatic malignancies, metastasized HCC, or other severe extrahepatic diseases (HCC without extrahepatic metastases or reduced life-expectancy < 1 year due to cirrhosis are not regarded as exclusion criteria).
Treatment with a PPI single standard dose/day or less for at least 7 days prior to screening.	Regular intake of NSAID on a daily basis (except for ASA 100 mg/day orally)
Females/males who agree to comply with the applicable contraceptive requirements.	One or more of the following measurements at the time of screening or documented up to 48 h before: ● Temperature > 38.5 °C ● Systolic blood pressure < 90 mmHg and heart rate > 100 bpm ● Catecholamine treatment > 0.1 μg/kg/min (terlipressin is allowed) ● Respiratory rate ≥ 22/min
Non-pregnant, non-lactating females.	Hypersensitivity or intolerance to esomeprazole, substituted benzimidazoles or other excipients of the IMP.
Ability to understand the patient information and to personally sign and date the informed consent to participate in the study, before completing any study-related procedures.	Ongoing therapy with nelfinavir.
The patient is co-operative and available for the entire study.	Participation in a clinical trial or use of an IMP within 30 days or five times the half-live of the IMP—whichever is longer—prior to receiving the first dose within this study.
Provided written informed consent.	Positive urine pregnancy test at screening or positive serum pregnancy test before the first treatment or is breast feeding.
	Patient is not willing to use adequate contraceptive precautions during the study and up for 5 days after the last scheduled dose of IMP.

*EGD* oesophago-gastro-duodenoscopy, *PPI* proton-pump inhibitors, *HCC* hepatocellular carcinoma, *NSAID* non-steroidal anti-inflammatory drugs, *ASA* acetylsalicylic acid, *IMP* investigational medicinal product

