**Methods:**

The STOPPIT-trial is a prospective, multicentre, randomized, double-blinded, placebo-controlled, parallel-group trial. In total, 476 patients with complicated liver cirrhosis who already receive long-term PPI therapy without evidence-based indication are 1:1 randomized to receive either esomeprazole 20 mg (control group) or placebo (intervention group) for 360 days. Patients with an indication for PPI therapy (such as a recent diagnosis of peptic ulcers, severe reflux esophagitis, severe hemorrhagic gastritis, recent endoscopic therapy for oesophageal varices) are excluded. The primary composite endpoint is the time-to re-hospitalization and/or death. Secondary endpoints include rates of re-hospitalization, mortality, occurrence of infections, hepatic decompensation and acute-on-chronic liver failure. The safety endpoint is defined as manifestation of an evidence-based indication for PPI re-therapy. The impact of PPI continuation or discontinuation on the intestinal microbiota will be studied. The recruitment will take place at 18 study sites throughout Germany. Recruitment has started in April 2021.

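### Table 1's exclusion for recent LA grade C or D reflux oesophagitis does not catch patients with 8 weeks or more of PPI before screening, so a severe lesion found on PPI days earlier does not prevent randomization to withdrawal

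*Protocol article*

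**What the plan says.** The text of Eligibility criteria {10} gives the intent: patients with an evidence-based PPI indication, for example "recent diagnosis of severe reflux esophagitis (LA grade C or D) or peptic ulcers are excluded". The Methods paragraph of the abstract says the same, listing indications "such as a recent diagnosis of peptic ulcers, severe reflux esophagitis, severe hemorrhagic gastritis". Neither statement carries a condition about earlier PPI use. The first refers to Table 1 for details, and the legend of Fig. 1 states: "Full in- and exclusion criteria are to be found in Table 1".

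Table 1 then gives the operative rule. It excludes LA grade C or D found by EGD less than 2 months before screening, with the added condition "without PPI therapy for at least 8 weeks prior to the screening visit". The next exclusion has no such condition: "Peptic ulcers diagnosed by EGD < 28 days prior to the screening visit".

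Three inclusion criteria bear on the point:
- "Treatment with PPI for at least 28 days prior to screening"
- "Treatment with a PPI single standard dose/day or less for at least 7 days prior to screening"
- "Hospitalization or recent hospitalization (0 to 42 days prior to the baseline visit) with complications of liver cirrhosis"

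In Table 2 (section {11b}), LA grade C or D on EGD after randomization is a safety endpoint. It counts as an evidence-based reason to resume PPI, and study medication stops. The Discussion says the exclusions represent evidence-based PPI indications and that withdrawal might harm such patients.

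**The concern.** Both time limits in the criterion end at screening, and nothing links the PPI course to the lesion. PPI taken before the EGD counts in full towards the 8 weeks. A severe lesion that appeared despite months of PPI is therefore treated as if it had already received a healing course.

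The trial recruits long-term PPI users, so the escape clause falls on its target population. A finding that would end study medication the day after randomization need not prevent randomization the day before. The risk falls on the placebo arm, half of those randomized, because the control arm continues esomeprazole 20 mg.

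**Working it through.** No figure in the plan is at issue, so there is nothing to reproduce. The check is to apply the criterion as worded.

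**Inputs** (all from Table 1)
- *d* = days from EGD to screening. Two calendar months are 59 to 62 days, so less than 2 months means *d* = 0 up to 58, or up to 61 at most. That is 59 to 62 possible values.
- *p* = days of PPI before screening, with *p* ≥ 28 by the inclusion criterion.
- 8 weeks = 8 × 7 = 56 days.

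**Two readings of the qualifier**
- Reading A, the patient lacks 8 weeks of PPI before screening: excluded if *d* < 2 months and *p* < 56.
- Reading B, the patient has been free of PPI for 8 weeks before screening: no includable patient can meet this, because inclusion requires *p* ≥ 28. The exclusion is then empty.

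**Number of values of *d*, out of 59 to 62, on which the patient is excluded**

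| Rule | *p* = 28 to 55 | *p* ≥ 56 |
|---|---|---|
| Printed, reading A | all 59 to 62 | 0 |
| Printed, reading B | 0 | 0 |
| Qualifier dropped | all 59 to 62 | all 59 to 62 |
| 8 weeks of PPI completed since the EGD | all 59 to 62 | 56 (*d* = 0 to 55) |

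Under the last rule, a patient with *p* ≥ 56 is admitted only from *d* = 56 onwards: 59 − 56 = 3 to 62 − 56 = 6 values.

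**Example.** A patient has taken PPI for 90 days, and an EGD 3 days before screening shows grade C. Here *d* = 3 and *p* = 90. The printed rule does not exclude this patient under either reading; both corrected rules do.

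**Hospitalization window.** Suppose the lesion is found within the 42 days before baseline. Screening is never after baseline, so *d* ≤ 42 < 56. Eight weeks of treatment since diagnosis cannot have been completed by screening. The wording still admits the patient if earlier PPI use brings *p* to 56.

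**Dose criterion.** If the PPI dose was raised above standard after the finding, the patient must be back on a single standard dose or less for 7 days before screening. This delays entry but does not prevent it.

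**The case against.** The best defence is that the intent is clear. The sentence above Table 1 excludes recent grade C or D disease, and the qualifier was probably meant to require 8 weeks of healing treatment for that lesion. On this view the row is loosely drafted and no one chose to admit these patients. That is likely true of the intent, but the sentence refers to Table 1 for details, so it exposes the contradiction without resolving it.

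Other points have some weight:
- The article is based on protocol version 2.0, which is not shown. Sites work from that document, and its wording may differ. This limits certainty about conduct, but the criterion as published is still wrong.
- The qualifier is ambiguous. That patients with 28 to 55 days of PPI stay excluded holds under reading A only. The gap for 56 days or more exists under both readings.
- The comparisons are not exact. Peptic ulcer is a different lesion with a different window, and Table 2 concerns a lesion found on study medication. The Discussion does not specifically address withdrawal after 8 weeks of PPI in grade C or D disease.
- The 14-day taper, the day-14 call, the day-28 visit, sucralfate, PPI re-therapy after a confirming EGD and DSMB review limit the consequences. All of them act after randomization and leave the entry rule as it is.
- An investigator may decline such a patient, but no listed criterion requires it.

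**Conclusion.** The concern holds. As printed, a patient with at least 56 days of PPI and LA grade C or D found at any time in the 2 months before screening is not excluded on account of that lesion. This is true under either reading of the qualifier and for any length of 2 months from 59 to 62 days. The rule contradicts the protocol's own intent and its treatment of the same lesion after randomization.

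The effect is on participant safety at entry. The document gives neither the distribution of PPI duration nor the share of patients with a recent grade C or D finding, so the number affected is unknown and may be small. It should be corrected. The conclusion rests on the published table; if version 2.0 of the full protocol words this row differently, the error is confined to the article.

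**What to change.** Preferred: drop the qualifier, so that the row excludes LA grade C or D reflux oesophagitis on an EGD less than 2 months before screening, whatever the earlier PPI use. This matches the form of the peptic ulcer row.

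Alternative: keep a qualifier that counts from the lesion, exempting only patients who have completed at least 8 weeks of PPI since that diagnosis. For patients with 56 or more days of PPI the two versions differ on only 3 to 6 days of the window, so the first is simpler and loses little.

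The cost is one change to the eligibility wording, plus a few patients lost or delayed by up to about 2 months after the EGD. Recruitment began in April 2021. Under section {25}, a substantial change needs ethics committee and authority approval and may require a revised consent form. If the full protocol already carries the intended rule, a note-to-file and a correction to the article may be enough.

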### Outcomes {12}

The primary composite endpoint is the time to unplanned re-hospitalizations or death during the trial period. However, expected re-hospitalization for mere paracentesis (without other complication of cirrhosis) during a period of 30 days after discharge is not regarded as an “unplanned re-hospitalization”. If the local investigator and the clinical trial management come to a conflicting assessment whether a re-hospitalization was “planned” or “unplanned”, a blinded endpoint committee (consisting of three independent hepatologists) will resolve this disagreement.

Secondary endpoints are described in Table 2. Importantly, patients who reach the primary endpoint “re-hospitalization” will continue all study procedures and will further receive the study medication. Therefore, secondary endpoints will be studied after a study participant has reached the primary endpoint. Patients who reach the safety endpoint (evidence-based re-therapy with PPI; see Table 2) are censored at the respective time-point.

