### Participant timeline {13}

Recruitment is planned to be completed within three years. With a trial duration 360 days per patient, time of first-patient-in to last-patient-out is four years. Figure 1 provides an overview of the trial design. After completion of the informed consent process, the screening visit will take place. Randomization will take place 0 to 14 days after screening during the baseline visit (visit 1, day 0). The study is split into two parts: “dose tapering phase” (days 1–14; tapering of the PPI dose in a blinded fashion, see above) and “main study phase” (days 15–360). Study visits and telephone interviews take place at the time-points indicated in Table 3. Study procedures during the respective visits and telephone interviews are summarized in Table 4.

**Table 3 Tab3:** Visits and time points

Screening visit	Up to 14 days before baseline
**Visit 1 (baseline)**	Day 0
**Visit 2**	Day 28 (± 2 days)
**Visit 3, 4, 5, 6**	Day 90, 180, 270, 360 (± 7 days, respectively)
**Telephone interview 1**	Day 14 (± 2 days)
**Telephone interview 2, 3**	Day 135, 225 (± 7 days, respectively)

**Table 4 Tab4:** Study procedures

Procedure	Screening	Baseline visit	Visits 2–6	Telephone interviews
Informed consent	X			
In-/exclusion criteria	X			
Randomization		X		
Medical history/demographics	X	X		
Adverse events/concomitant medication/endpoint assessment		X	X	X
Physical examination/height and weight		X	X	
Vital sign assessment	X	X	X	
Laboratory (haematology, biochemistry)		X	X	
Pregnancy test	X			
Stool samples & biobanking		X	X (visit 3)	
Ultrasound		X	X (visit 4, 6)	
Distribution and/or return of study medication and patients diaries		X	X	

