### Recruitment {15}

Patients will be recruited at the trial centres during or after hospitalization. Global and local recruitment rates will be monitored by the clinical project management and the data safety and monitoring board (DSMB). Trial sites are obliged to recruit a number of patients according to their respective pre-study prognosis. In case trial sites do not fulfil these obligations in a specified time, countermeasures can be taken (e.g., direct communication with the investigator, addendum to the protocol).

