## Assignment of interventions: allocation

### Sequence generation {16a}

Randomization will be carried out locally. A block randomization procedure with variable block length will be applied stratified for the study centres and severity of liver cirrhosis (MELD score ≤13 or > 13). Blinding of therapy for the patients and the investigators will be ensured by identical encapsulation of placebo and esomeprazole 20 mg that makes both indistinguishable, and by the use of identical medication packages. Unique randomization codes labelled on the medication packages ensure the specific allocation of the study medication to the study participant.

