## Statistical methods

### Statistical methods for primary and secondary outcomes {20a}

The primary efficacy endpoint analysis will be performed according to the intention-to-treat (ITT) principle based on the full analysis set (FAS). The effects of continuation or discontinuation of PPI therapy with respect to the primary endpoint will be estimated and tested by Cox regression. The regression model will include treatment arm and categorized the severity of cirrhosis (MELD ≤ 13 vs. > 13) as fixed effects and the study centre as a random effect. As an estimated effect size, the hazard ratio (HR) between the two treatment arms will be given with the corresponding 95% confidence interval. The one-sided test of the superiority of discontinuation of PPI over the continuation of PPI at significance level 2.5% will be based on the corresponding asymptotic two-sided 95% confidence interval from the Cox regression model. The null hypothesis is rejected if the upper limit of the confidence interval is below 1.0. The analysis of the treatment effect with respect to the individual components of the composite endpoint and to secondary endpoints will be performed analogously with the (cause-specific) Cox model. Time to event outcomes will be visualized by Kaplan-Meier curves stratified by treatment group. Adverse event data will be summarized by the treatment group.

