## Discussion

Prophylactic long-term PPI treatment without evidence-based indication is frequently regarded as “common use” in daily clinical routine in patients with liver cirrhosis [1–9]. Increasing evidence from observational studies suggests possible harmful effects of chronic PPI treatment in cirrhotic patients. However, the negative impact of chronic PPI treatment on infection rates [8–16, 21–23], rates of hepatic decompensation [6, 7, 9, 28, 29], hospitalization rates [20, 30, 31] and mortality of cirrhotic patients [5, 6, 10, 32, 33] remains controversial due to conflicting data [4, 24–27]. Therefore, it remains unclear if PPI use is causative for patient mortality or merely associated with comorbidities which themselves lead to a higher mortality in patients [51, 52]. On the other hand, patients with liver cirrhosis are at an increased risk of variceal and nonvariceal gastrointestinal bleedings [37–44] and PPI could have preventive effects.

The primary aim of this study is to prove superiority of PPI discontinuation over continuation in (recently) hospitalized liver cirrhosis patients without evidence-based indication for PPI use with regard to the composite primary endpoint “death and/or unplanned re-hospitalization”. As the above-mentioned complications regularly lead to a hospitalization of cirrhotic patients and a hospitalization itself is considered a risk factor for mortality in patients with liver cirrhosis [50], re-hospitalization is an adequate surrogate for patient-relevant complications of liver cirrhosis. By aggregation of unplanned re-hospitalization and mortality to a composite endpoint, we avoid underestimation of clinically significant events resulting in pre-clinical mortality. However, this implies a risk that mortality will be underrepresented in the primary results, as most fatal outcomes are expected to occur after re-hospitalization. Thus, incidence of secondary endpoints including mortality will be studied after re-hospitalization. We will not regard expected re-hospitalization due to ascites (without SBP or other complications) during a period of 30 days after discharge as a primary end-point criterion, as patients with refractory ascites are often expected to be re-hospitalized for paracentesis.

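### Patients randomised while still in hospital can have only death as a primary event until discharge, and the primary model ignores in-hospital status: a small effect with a cheap, optional remedy

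*Protocol article*

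**What the plan says.** Table 1 (Eligibility criteria {10}) requires "Hospitalization or recent hospitalization (0 to 42 days prior to the baseline visit) with complications of liver cirrhosis". Recruitment {15} confirms the mix: "Patients will be recruited at the trial centres during or after hospitalization". Participant timeline {13} places randomisation at the baseline visit on day 0, up to 14 days after screening, and does not require discharge first.

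Outcomes {12} states: "The primary composite endpoint is the time to unplanned re-hospitalizations or death during the trial period". The one event it exempts is "expected re-hospitalization for mere paracentesis (without other complication of cirrhosis) during a period of 30 days after discharge". It gives no rule for a complication in, or a prolongation of, the stay during which a patient was randomised (the index stay). The Discussion defends the endpoint on the ground that "re-hospitalization is an adequate surrogate for patient-relevant complications of liver cirrhosis".

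Sequence generation {16a} stratifies by centre and MELD category. For the analysis, Statistical methods {20a} says: "The regression model will include treatment arm and categorized the severity of cirrhosis (MELD ≤ 13 vs. > 13) as fixed effects", with centre as a random effect. In-hospital status is in neither place, nor among the subgroups listed under {20b}.

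**The concern.** Take two patients who develop an infection or encephalopathy on day 5. The one already discharged is admitted and has a primary event. The one still in the ward has none unless he dies, and his longer stay then passes as event-free time. The surrogate argument in the Discussion works only for patients who can be admitted, so it does not cover an inpatient until discharge.

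Two things are at stake. First, an arm with longer index stays gains event-free time in the composite. Second, inpatients and discharged patients may differ in prognosis. If they do, a Cox model that pools them gives a hazard ratio pulled towards 1.

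**Working it through.** **Inputs from the article (Sample size {14}):** event rates at 6 months of 65% (control) and 50% (discontinuation), two-sided alpha 5%, power 80%, 184 events, 476 patients, 360 days of follow-up, 20% loss.

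**Assumed, because the article gives neither:** inpatient share f of 30% to 70%; exponential remaining stay with mean m of 7 or 14 days. Other assumptions are named where used. The article does not state the time origin in so many words; day 0 is the natural reading.

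**1. The plan's own figure.** HR = ln(0.50)/ln(0.35) = 0.660. Events (Schoenfeld) = 4 × (1.960 + 0.842)² / (ln 0.660)² ≈ 183; Freedman's formula gives 188. The stated 184 is reproduced and is not in dispute.

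**2. Share of first complications that cannot count.** Daily hazards are −ln(0.35)/182.5 = 0.00575 (control) and −ln(0.50)/182.5 = 0.00380 (discontinuation). For an inpatient with hazard λ, the chance that the first complication precedes discharge is λ/(λ + 1/m). The chance of one within 360 days is 0.874 and 0.745, mean 0.810.
- f = 30%, m = 7: chances 0.0387 and 0.0259, mean 0.0323; 0.30 × 0.0323 / 0.810 = 1.2%.
- f = 70%, m = 14: chances 0.0745 and 0.0505, mean 0.0625; 0.70 × 0.0625 / 0.810 = 5.4%.
- If the hazard in hospital were three times as high (assumed), the range would be about 3% to 14%.

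**3. Power.** With 20% exponential dropout over 360 days, 476 patients give about 356 events. Shares of 25% to 100%, stays of 7 to 28 days and only 10% of the hazard (deaths) active in hospital (all assumed) lower this to between 355 and 342, still far above 184.

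**4. Unequal index stays.** Simulation of 400,000 patients with a mean stay of 14 days under discontinuation and no primary events during the stay, a simplification that ignores in-hospital deaths.

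| Mean control stay (days) | HR, no true effect: half inpatients / all | HR, true 0.66: half / all |
|---|---|---|
| 17 | 1.01 / 1.02 | 0.67 / 0.67 |
| 21 | 1.03 / 1.05 | 0.67 / 0.69 |
| 28 | 1.04 / 1.10 | 0.69 / 0.72 |

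Longer control stays move the HR upwards, against discontinuation.

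**5. What a stratum does.** Half inpatients, true HR 0.66. With equal prognosis, stratified and unstratified estimates agree. With the inpatient hazard doubled (assumed), the unstratified HR is about 0.68 and the stratified HR 0.66 to 0.67, so most of the attenuation goes.

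**The case against.** The case for leaving the plan alone is substantial, and most of it stands.

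- **Size.** With equal stays and equal prognosis, the unstratified HR stays at 0.659 to 0.661 against a true 0.660. This stands.
- **Bias.** Randomisation balances the inpatient share in expectation, so leaving it out of the model does not inflate type I error. This stands. Distortion needs treatment to alter the index stay.
- **Taper.** On days 1 to 14 the discontinuation arm still takes esomeprazole on 6 of 14 days (Intervention description {11a}). The treatment contrast is therefore weakest when most index stays would end. This stands, and it makes any early effect that goes uncounted smaller.
- **Captured elsewhere.** Death in the index stay is a primary event. Infections, decompensation, ACLF and bleeding are secondary endpoints with no out-of-hospital condition, and prolonged hospitalization is an SAE criterion {22}. A reader might infer that these complications are lost to the trial; they are missing only from the composite.
- **The stratum.** It cannot turn an index-stay complication into an event. This stands, and is why a second analysis is needed.
- **Article scope.** Finer event rules may sit in the full protocol. That is fair for a missing rule. The point here rests on the eligibility, endpoint and model terms that the article does fix.

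A reader might also set 50% at 3 months beside 65% at 6 months and conclude that the hazard halves after month 3, so that inpatients and discharged patients start on different parts of a known curve. The article does not support this. The first figure is re-hospitalization alone, counted from discharge; the second is the composite with death in the control group. They are not two points on one curve. Nor does allowing terlipressin or low-dose catecholamines at screening show that remaining stays are long; the article gives no length of stay.

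**Conclusion.** The point holds as a minor, optional improvement. From the text alone, patients still in hospital can be randomised, only death can be a primary event for them before discharge, and the primary model ignores that status. About 1% to 6% of first complications would go uncounted, and this range rests on the assumed inpatient shares and stays and on a constant hazard.

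Reading this as a threat to validity goes too far. Power is ample, type I error is not inflated by the omitted factor, and the overall HR hardly moves unless stays differ between arms or prognosis differs by status. Longer control-arm stays, which the trial's own hypothesis makes plausible, would make the result conservative for discontinuation. Longer stays under discontinuation would act the other way.

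**What to change.** Two prespecified additions, made before unblinding:

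1. Add in-hospital status at randomisation (inpatient or discharged on day 0) to the primary Cox model as a stratum, so that each group has its own baseline hazard. The purpose is to gain precision and avoid attenuation if prognosis differs; under equal prognosis it costs essentially nothing.
2. Prespecify days alive and out of hospital to day 360 as a supplementary analysis of the composite, counting the rest of the index stay as days in hospital. This is the part that makes prolongation count against the arm in which it occurs.

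The cost is a little more analysis work. Status is known at randomisation, and the second analysis needs admission and discharge dates, so check that the index discharge date is recorded for patients randomised as inpatients. The primary endpoint, sample size and visit schedule do not change.
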